## Methods/Design

### Study objective

The EPIOSA study has the following specific aims: 1) Use of questionnaires, sleep studies, carotid ultrasonography and cerebral magnetic resonance imaging (MRI) for the definition of OSA subpopulations and controls among individuals without comorbidities; 2) Identification and definition of the parameters that predict disease progression over 5 yrs of follow-up. For the purposes of the present study, disease progression is defined in terms of changes in sleep disordered breathing variables, symptoms, carotid artery intima-media thickness (IMT) and plaque and new microblebs in MRI; 3) Identification of useful biomarkers for disease progression by measuring known biomarkers that correlate with OSA severity, in blood and urine samples; 4) Identification of novel epigenetic factors and/or biomarkers correlating with poor outcomes in OSA and controls. This will be analyzed by cytometry analysis, DNA methylation in genes subserving inflammatory functions RNA transcriptomics; and 5) assessment of the effect of CPAP (Continuous positive airway pressure) on inflammatory and epigenetic mechanisms and disease progression.

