### Study design

EPIOSA is a 5-yr non-interventional longitudinal prospective study being conducted at the Sleep Clinic of the Hospital Universitario Miguel Servet, a large teaching hospital in Zaragoza (Spain). Following a baseline visit, subjects are to be followed-up at 3, and then every year. All subjects will continue to receive their usual care by their primary physician and sleep specialist throughout the study. CPAP treatment will be started according to the Spanish National guidelines, free of cost for the patients [18].

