### Statistical analyses

Groupwise comparisons (n >2) will be performed using a nonparametric Kruskal-Wallis test followed by a Mann–Whitney U test as appropriate. Pairwise comparisons were performed using a nonparametric Mann–Whitney test unless otherwise indicated. Chi square tests will be performed for categorical variables. Regression models will be applied to assess the effect of OSA, biomarkers, peripheral lymphocytes and epigenetic changes on CIMT, carotid plaque and cerebral microbleeds. All models will be adjusted for age and BMI, and additionally for covariables that may change the estimated risk beyond 5% Specific statistics procedures will be performed for the arrays as described above. STATA-12 for Windows (STATA CORP, TX, USA) are to be used for all analyses.

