There are many potential mechanisms linking OSA, endothelial dysfunction, atherosclerosis and cardiovascular diseases. Sleep loss and fragmentation could trigger endothelial dysfunction and immune response but its remains to be demonstrated if this occurs in patients with OSA. Chronic intermittent hypoxia (CHI) is the other hallmark of OSA. CIH can induce endothelial dysfunction independently of respiratory effort in animal models [37]. In patient with OSA, oxygen desaturation index (ODI), a surrogate of CHI severity has been associated with endothelial dysfunction [38]. On the other hand, ODI emerged as an independent predictor of carotid and aortic wall thickness in OSA patients using cardiovascular magnetic resonance study [39]. CPAP treatment of OSA significantly reduces carotid intima-media thickness, supporting the concept that OSA is an independent risk factor for atherosclerosis [31]. There is growing evidence that OSA is associated with increased activation of immune and inflammatory cells including circulating monocytes, platelets and lymphocytes and proinflammatory cytokines such as leukotrienes, interferon-γ, TNF-α and IL-6 have been reported elevated in OSA [8]. CRP levels have been particularly studied with conflicting results [7,40]. The intermediate process for an increased risk of atherosclerosis in OSA could be the presence of this systemic inflammation and immunity activation as a result of the CHI. There is no evidence of genetic alterations in patients with OSA that favor the development of systemic inflammation, changes the adaptive immunity or that specifically encourage the emergence of early atherosclerosis. However, it is likely a different response from the pro-inflammatory genes to CIH. This response depends in part on epigenetic mechanisms that promote or suppress the expression of these genes. Recently in pediatric OSA those children with elevated CRP, were more likely to have increased DNA methylation of the FOXP3 gene [16]. This result in a reduced Treg population and in a swift Th1:Th2 balance towards Th1 predominance [29]. These immune-inflammatory changes favor endothelial dysfunction and a pro-atherogenic state and ultimately an increased risk for cardiovascular diseases. If those mechanisms also play a role in accelerated atherosclerosis in adults with sleep apnea is unknown. In conclusion, the current study is novel in several ways: 1) It is the first study to evaluate the relationship between baseline OSA phenotypes and normal matched controls without comorbidities and subclinical atherosclerosis and 2) it will allow prospective analysis of inflammatory biomarkers, as well as methylation and miRNA abnormalities in non-OSA subjects and patients with treated or non-treated OSA. Our results may provide more information on the association of OSA and cardiovascular diseases and possibly identifying novel targets for therapeutic intervention. It could also provide evidence that CPAP can not only improve daytime symptoms, but also have a positive effect on progression of subclinical atherosclerosis.

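### The CPAP contrast is not randomised, yet as written it may be tested unadjusted or with only age and BMI assured, and the 5% covariate rule cannot keep mediators out of the OSA models

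*Protocol article*

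**What the plan says.** The Study design section describes the study thus: "EPIOSA is a 5-yr non-interventional longitudinal prospective study". On treatment it says: "CPAP treatment will be started according to the Spanish National guidelines, free of cost for the patients". The guideline's criteria are not given.

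The fifth aim in Study objective is "assessment of the effect of CPAP (Continuous positive airway pressure) on inflammatory and epigenetic mechanisms and disease progression". Power considerations states power for one contrast only, IMT in CPAP-treated versus untreated OSA patients (80%, significance level 0.0125).

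Statistical analyses makes three statements that bear on this contrast:

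- Two-group comparisons use a Mann-Whitney test unless otherwise indicated.
- "Regression models will be applied to assess the effect of OSA, biomarkers, peripheral lymphocytes and epigenetic changes on CIMT, carotid plaque and cerebral microbleeds". CPAP is not in that list.
- "All models will be adjusted for age and BMI, and additionally for covariables that may change the estimated risk beyond 5" per cent.

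The Discussion reports that "ODI emerged as an independent predictor of carotid and aortic wall thickness in OSA patients", having called ODI a surrogate for the severity of intermittent hypoxia. It also proposes systemic inflammation and immune activation as the step between OSA and atherosclerosis.

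**The concern.** There are two separate problems.

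**The CPAP contrast.** Treatment follows clinical indication. If the indication tracks severity, and severity predicts wall thickness as the Discussion reports, treated and untreated men differ at baseline in something that affects the outcome. A Mann-Whitney test on follow-up IMT does nothing about this. A regression with age and BMI removes only the part that BMI carries. A real benefit of CPAP could be hidden, or could appear as harm. The Discussion hopes for evidence of a favourable CPAP effect on progression, and that contrast could not supply it.

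**The OSA models.** A change-in-estimate rule asks only whether the coefficient moves. Confounders and mediators both move it. The study measures hsCRP, cytokines and T-cell subsets, and nothing in the rule bars them as covariates in a model for the effect of OSA. Including them would remove part of the total effect that the model is meant to estimate.

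**Working it through.** **1. The plan's own figures.** Attrition reproduces: 300 × 0.98^5 = 271.2 and 50 × 0.98^5 = 45.2, against 270 and 45 stated. The 80% power does not reproduce if the stated 2 SD is the difference: about 5 to 6 men per group would then suffice, and 270 give power near 100%. That is a separate matter. As a yardstick here, the difference detectable with 80% power at two-sided 0.0125 among 270 patients is (2.498 + 0.842) × √(1/n1 + 1/n2). This gives 0.41 SD at 135/135 and 0.51 SD at 54/216. The actual split is not stated.

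**2. What adjustment the CPAP contrast is assured.** By the default pairwise test, none. By regression, if it is applied to CPAP at all, age and BMI. Severity, symptoms and baseline CIMT enter only if someone nominates them as candidates and they pass the 5% rule.

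**3. Possible size of confounding.** All inputs are assumed, and the total outcome SD is a little under 1.

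- True CPAP effect: -0.20.
- Slope of IMT on severity, g: 0.1 to 0.3 per SD of severity.
- Correlation of severity with BMI: 0.4; slope of IMT on BMI: 0.1.
- Log-odds of CPAP: 1 to 3 per SD of severity, which gives a severity gap between treated and untreated men of 0.83 to 1.38 SD.

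Unadjusted, bias = (g + 0.1 × 0.4) × gap:

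- Low end: 0.14 × 0.83 = 0.12, so the estimate is about -0.08.
- High end: 0.34 × 1.38 = 0.47, so the estimate is about +0.27.

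By simulation of the same model:

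- Age and BMI only: -0.13 to +0.17.
- Severity added: -0.20 to -0.21.

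**4. If severity is a candidate under the 5% rule.** With n = 270, slopes of 0.1 to 0.3 and log-odds of 1 or 2, the rule selects severity in 96% to 100% of simulated samples.

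**5. Mediators in the OSA model.** Assume a total OSA effect of 0.3 SD, with a share f passing through a marker. Adjusting for the marker leaves 0.3 × (1 - f), so the coefficient changes by a fraction of about f. Simulated:

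| Share mediated | Unadjusted | Adjusted for marker | Change |
|---|---|---|---|
| 5% | 0.295 | 0.280 | 4.9% |
| 10% | 0.301 | 0.268 | 11% |
| 20% | 0.292 | 0.232 | 21% |
| 50% | 0.293 | 0.146 | 50% |

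A marker carrying clearly more than 5% of the effect therefore passes the rule, and the total effect shrinks by that share.

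**6. Precision cost of adjusting for severity.** At a 1:1 split and an assumed severity gap of 1.5 SD, the correlation of treatment with severity is 1.5 × 0.5 = 0.75. The variance inflation is 1 / (1 - 0.75²) = 2.29, and the detectable difference becomes 0.406 × √2.29 = 0.61 SD. At a gap of 0.83 SD the correlation is 0.415, the inflation is 1.21 and the detectable difference is 0.45 SD.

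**The case against.** **Not forcing severity in is not leaving it out.** A reader might infer that any regression under this rule will be biased for CPAP. The documents do not support that. A severity measure that confounds materially would almost always pass the 5% rule if offered (step 4). The confounding in step 3 arises only if CPAP is judged by the unadjusted test, or if severity is never a candidate. The text permits both and states neither. This objection stands, and it limits the point to what can happen.

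**Chance selection of covariates.** A reader might also object that a relative 5% threshold fires on noise. It does: a pure-noise covariate passed in about 29% to 43% of samples. But adjusting a linear model for a covariate unrelated to group does not bias the estimate, so this is no evidence of harm.

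**Severity in the OSA-versus-control comparison.** It may seem that severity confounds this comparison too. It does not, because AHI defines the groups. For that comparison only the mediator point remains. Even there, the text lists biomarkers and lymphocytes as exposures in their own right and does not say they will be covariates; it merely does not exclude them. A mediator-adjusted estimate would also be legitimate if a direct effect were intended, but the text does not say which effect is meant.

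**Existing safeguards.** Smoking, hypertension, dyslipidaemia, diabetes, vascular disease and chronic oral therapy are excluded at entry, and controls are matched on BMI. These limit other confounding, but none balances severity between treated and untreated OSA patients.

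**A condensed article.** Candidate covariates and mediation models may sit in a fuller plan. That is fair for what the article omits. It does not answer the rule the article fixes for all models, since a longer candidate list under the same rule could still admit mediators.

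**Conclusion.** The point holds in limited form. The article makes the effect of a non-randomised treatment an aim and powers a contrast on it. It then assures that contrast of no more than age and BMI, and possibly of no adjustment at all. The CPAP estimate can be confounded. Under the assumed inputs the bias runs from about 0.1 to 0.5 SD unadjusted and from about 0.07 to 0.37 SD with age and BMI, against a detectable difference of 0.41 SD at a 1:1 split. Size and direction both rest on assumptions the documents do not supply, chiefly that guideline treatment follows severity. The Discussion supports only the link from hypoxia severity to wall thickness.

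For the total effect of OSA, the 5% rule can admit markers on the article's own hypothesised pathway and attenuate the estimate by roughly the share they carry. That share is unknown.

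**What to change.** **CPAP contrast.** State that the main analysis is a regression, or a propensity- or overlap-weighted comparison, with a fixed set of baseline covariates: AHI and/or ODI, Epworth score, age, BMI and baseline CIMT. Let this replace the Mann-Whitney test for the contrast, and report the result as an association.

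**Other total-effect models.** Replace the 5% rule by a fixed list of baseline confounders. Keep inflammatory markers, T-cell subsets, methylation and all post-baseline values out of these models, and use them in mediation models declared as such. Do not add AHI or ODI as a confounder when comparing OSA with control.

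**Cost.** The change is to analysis wording. The sleep study with oximetry, Epworth score, BMI and carotid ultrasound are already scheduled at baseline. The real price is precision for the CPAP contrast when treatment and severity are closely related: the detectable difference rises from about 0.41 to about 0.6 SD at an assumed 1.5 SD severity gap, and to about 0.45 SD at a gap of 0.83 SD. Adjusting for baseline CIMT may recover some of this, by an amount the documents do not allow one to calculate.

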At baseline and every year, whole blood samples are drawn using a 21G butterfly needle into serum gel, EDTA, sodium fluoride and PaxgeneW tubes (PreAnalytix GmbH, Switzerland). Serum glucose, triglycerides, total cholesterol and HDL cholesterol will be measured by spectrophotometry (Chemical Analyzer ILAB 650, Instrumentation Laboratory), and serum apolipoproteins A and B, will be measured by kinetic nephelometry (Immunochemistry Analyzer IMMAGE 800, BeckmanCoulter). Within two hours after collection, high sensitive C-reactive protein (CRP) will be measured based on a particle-enhanced turbidimetric immunoassay technique. For biobanking, about 15 ml of EDTA blood and 5 ml of blood without anticoagulant for serum preparation are to be fractionated into plasma, serum and whole blood and in 1 ml dot-coded metal-free cryotubes are to be stored at -80°C. Inflammatory markers to be assessed are shown in Table 2.

**Table 2 T2:** Outcome measurements in the Epigenetics in Obstructive Sleep Apnea (EPIOSA) study

**Measurement**	**Description**	**Frequency of assessment**
Questionnaires, Dietary, Epworth Sleepiness Scale		Each visit
Vital signs	Including sitting blood pressure, heart rate, height and weight	Each visit
Exhaled carbon monoxide	Confirmation of smoking status	Each visit
Spirometry	Post-bronchodilator FVC, FEV1 and FEV1/FVC	Baseline
Electrocardiogram	12-lead resting electrocardiogram	Baseline
Sleep Study	At home type 3 monitor for diagnosis and at home autoCPAP for CPAP titration (if appropriated)	Baseline and every year
Blood sample	Standard biochemistry and lipid markers: Total cholesterol, LDL, HDL, TG, Apo A, Apo B.	Baseline and last visit
	Inflammatory markers: TNF-α, IFN-ϒ, IL-1β, IL-6, IL-8, IL-10.	
Urine sample	Microalbuminuria, 8-isoprostane	Baseline and every year
Carotid Ultrasonography	High-resolution B-mode assessment of carotid artery intima-media thickness and plaque	Baseline and every year
Magnetic resonance imaging	Cerebral microbleeds detection	Baseline and last visit
Flow cytometry	Fresh peripheral blood T-cell phenotype	Baseline and last visit
DNA methylation	Genome-wide DNA methylation status	Baseline and last visit
miRNA microarray analysis	Levels of candidate miRNAs regulated by aberrant DNA methylation	Baseline and last visit

#### **
*Flow cytometry*
**

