At baseline, whole fresh blood with EDTA will be obtained for flow cytometry. Table 3 shows the cells stained, and also the antibodies and kits used. The samples will be incubated for 15 min at room temperature, then acquired in a GALLIOS flow cytometer (Beckman Coulter) and analyzed with the KALUZA software (Beckman Coulter).

**Table 3 T3:** Subset of T cell population to be analyzed

**Antibody-kit**	**Clone**	**Fluorescence**	**Catalog number**
CD4-CD8- CD3	CD4:HP2/6, CD8: 143–44, CD3: 33-2A3	CD4: FITC CD8: PE CD3: PERCP	4FI8PEI3PPI-50 T. IMMUNOSTEP
CD11c	BU-15	FITC	11CF3-100 T IMMUNOSTEP
CD14	47-3D6	APC	14A-100 T IMMUNOSTEP
CD15	MCS-1	FITC	15 F-100 T IMMUNOSTEP
CD16	3G8	PE	16PE2-100 T IMMUNOSTEP
CD45	HL30	CF BLUE	45CFB2-100 T IMMUNOSTEP
CD45 RA	HI100	APC	45RAA2-100 T IMMUNOSTEP
CD 62 L	DREG 56	APC-eFluor 780	47-0629 eBioscience
Human regulatory T cell cocktail*	CD4: SK3, CD25: 2A3, CD127: HIL-7R-M21	CD4: fitc, CD 25: PE-Cy7, CD127: Alexa fluor 647	560249 (BD Pharmigen)

*T reg was defined as CD4+/CD25+/CD127 (low/-) phenotype (ref. [23]).

#### **
*DNA methylation analysis*
**

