Part of the blood samples collected in EDTA tubes are stored at -80°C until DNA isolation, which is performed in the Department of Molecular Biology at the Faculty of Veterinary of the University of Zaragoza. Genomic DNA is obtained with the use of the illustra blood genomic Prep Midi Flow Kit (GE Healthcare, UK) following the manufacturer’s instructions. Genome-wide DNA methylation profiles will be studied in approximately 1 μg of genomic DNA treated with sodium bisulfite. The converted DNA will be analyzed using Illumina’s Infinium Human Methylation 450 BeadChip assay (Illumina, San Diego, CA, USA). To minimize position effects, cases and controls will be randomly distributed. The assay allows determination of DNA methylation levels at >450,000 CpG sites covering all designable RefSeq genes, including promoter, 5′, and 3′ regions. It captures CpG islands and shores, non-CpG methylated sites, microRNA promoter regions and disease-associated regions identified through genome-wide association studies [24]. Illumina array data will be processed using the Methylation Module of GenomeStudio v1.9 software. To identify differentially methylated regions (DMRs), we will use a 1-kb sliding window and apply Fisher’s method to combine P values for each 1-kb region on the basis of all probes within each window [25]. Significant DMRs will be selected at a 1% FDR on autosomes and 5% FDR on chrX. After statistical analyses, the methylation patterns of the gene of interest will be confirmed by sequencing of the 24 bisulfite-treated DNA samples used for the genome wide analysis.

#### **
*Gene expression analysis*
**

Blood samples stored at -80°C in PaxGene (TM) tubes will be used for total RNA isolation using PAXgene Blood RNA Kit (Qiagen, Venlo, Netherlands). Quantitative real time polymerase chain reactions (qRT-PCR) will be performed to test whether differential methylation patterns of the selected genes affect their expression level. Complementary DNA will be synthesized from total RNA using random hexamers and the SuperScript^®^ III First Strand Synthesis Kit (Life Technologies, Carlsbad, California, US). Primers and TaqMan^®^ probes will be selected from the Applied Biosystems Inventories Assays and qRT-PCR will be performed in a The StepOne™ Real-Time PCR System (Applied Biosystems, Life Technologies, Carlsbad, California, US).

#### **
*MicroRNA analysis*
**

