### Power considerations

The calculation of EPIOSA’s planned sample size of 300 patients and 50 matched controls, is based on three estimations: a) in pediatric patients, those with OSA (n = 37), showed a reduced Treg population and altered Th1:Th2 balance toward Th1 predominance compared with non-OSA controls (n = 13) [30]; b) differences among DNA methylation in inflammatory genes were observed among OSA patients with high hsCRP (n = 31), compared with normal non-OSA controls (n = 31) [16]; and C) a randomized study showed that effective treatment of OSA with continuous positive airway pressure for 4 months significantly decreases IMT as early signs of atherosclerosis in 24 patients with severe OSA [31]. We expected a loss to follow-up of an average of 2% per year. In this way at the end of the 5-year follow-up we hope to analyze outcomes in 270 patients with OSA and 45 without OSA. This sample size ensures to analyze subgroups of patients according with prescribed treatment for OSA. Specifically, the sample will have 80% power to detect average IMT differences when comparing OSA patient treated and non-treated CPAP. The power is calculated based on a 2 SD with a significance level of 0.0125.

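### Methylation in unsorted blood is compared with no stated adjustment for leukocyte mix, so a shift in cell proportions can be read as an epigenetic change

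*Protocol article*

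**What the plan says.** Three parts of the Protocol article bear on this.

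- **Material.** Under Laboratory analysis, "At baseline and every year, whole blood samples are drawn using a 21G butterfly needle into serum gel, EDTA, sodium fluoride" and other tubes. Under DNA methylation analysis, "Part of the blood samples collected in EDTA tubes are stored at -80°C until DNA isolation". No sorting or separation of cells is described before extraction.
- **Array procedure.** The same section fixes a 450K array and a 1-kb sliding window, with Fisher's method used to "combine P values for each 1-kb region on the basis of all probes within each window". The threshold is also fixed: "Significant DMRs will be selected at a 1% FDR on autosomes and 5% FDR on chrX". The only bias control stated is "To minimize position effects, cases and controls will be randomly distributed". Selected genes are then confirmed by sequencing the bisulfite-treated samples used for the genome-wide step, which the text counts as 24.
- **Statistical analyses.** For the arrays, "Specific statistics procedures will be performed for the arrays as described above". Adjustment for age and BMI, with a 5% change-in-estimate rule for further covariables, follows regressions whose outcomes are CIMT, plaque and microbleeds. Lymphocytes and epigenetic changes enter those models as exposures.

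On the expected biology, Power considerations cites children with OSA who "showed a reduced Treg population and altered Th1:Th2 balance toward Th1 predominance compared with non-OSA controls". On available cell data, the Flow cytometry section says "At baseline, whole fresh blood with EDTA will be obtained for flow cytometry". Table 2 lists both cytometry and methylation at baseline and last visit.

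**The concern.** Methylation measured in whole blood is an average over cell types, weighted by their proportions. At a CpG where two cell types differ, a change in their proportions moves the average even if nothing changes inside any cell. Random placement on the array protects against position effects but not against this.

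The study supplies its own reason to expect such a change. Power considerations and the Discussion both anticipate fewer Treg cells and a Th1 shift in OSA. The Discussion also refers to the FOXP3 region that is demethylated specifically in Treg cells, and reads its higher methylation as possible epigenetic suppression. In mixed blood, a lower Treg share alone would raise that signal.

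The study's hypothesis concerns epigenetic regulation. If the two explanations cannot be separated, a positive region cannot be credited to regulation.

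**Working it through.** **1. Does any stated adjustment reach the group comparison of methylation?** The array section names none. The age, BMI and 5% rule belongs to models in which methylation is a predictor, not the outcome. The default pairwise test, Mann-Whitney, takes no covariates. So no stated adjustment reaches it.

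**2. Would the planned confirmation detect the problem?** Sequencing reuses the same bisulfite-treated samples and therefore the same cell mix. The expression check uses RNA from PAXgene blood, for which no cell separation is described either. A cell-mix difference would tend to pass both.

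**3. How large could it be?** The plan states no figure to reproduce. The inputs below are assumptions unless marked otherwise.

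- Δβ, methylation difference between two cell types: 0.6 to 0.8
- s, shift in the cell fraction between groups: 0.05 or 0.02
- SD of the fraction within groups: 0.05 to 0.08
- residual SD of methylation: 0.03
- within-cell effect: none
- array size: 24 in total (from the document); the 12 v 12 split is assumed

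Apparent difference = Δβ × s. In SD units, d = Δβ × s / √[(Δβ × SD of fraction)² + 0.03²].

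For s = 0.05 the apparent difference is 0.030 to 0.040:

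| Δβ | SD of fraction | d | P<0.05 at 12 v 12 |
|---|---|---|---|
| 0.6 | 0.05 | 0.030/√(0.030² + 0.030²) = 0.71 | 38% |
| 0.6 | 0.08 | 0.030/√(0.048² + 0.030²) = 0.53 | 24% |
| 0.8 | 0.05 | 0.040/√(0.040² + 0.030²) = 0.80 | 47% |
| 0.8 | 0.08 | 0.040/√(0.064² + 0.030²) = 0.57 | 26% |

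For s = 0.02, d is 0.21 to 0.32 and P<0.05 occurs in 8% to 12%. These are two-sided two-sample t tests from the noncentral t distribution.

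**4. Simulation with and without the cell fraction.** Each setting had 4,000 runs with no within-cell change. An unadjusted Mann-Whitney test was compared with a linear model containing the measured fraction.

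| Marker (assumed) | Shift | Unadjusted, 12 v 12 | Unadjusted, 300 v 50 |
|---|---|---|---|
| Major fraction: 30%, SD 5 points, Δβ 0.8, residual SD 0.02 | 2 points | 0.11 | 0.63 |
| Same | 5 points | 0.51 | 1.00 |
| Treg-type: 1%, SD 0.3 points, Δβ 1.0, residual SD 0.01 to 0.02 | 0.25 to 0.5 points | 0.06 to 0.19 | 0.12 to 0.86 |

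The 0.51 exceeds the 47% in step 3 because the residual SD is smaller: d = 0.040/√(0.040² + 0.020²) = 0.89. The Treg-type shift moves mean methylation by only 0.0025 to 0.005. With the fraction in the model, the false-positive rate was 0.044 to 0.058 in every setting. That assumes the fraction is measured without error.

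**The case against.** **The article is condensed.** It never says which probe-level test produces the P values that are combined, and a covariate list could sit in a fuller document. This stands in part: the absence of adjustment is read from what is stated. But the article sets out this procedure down to window width and chromosome-specific thresholds, then names it as the method for the arrays. As written, nothing in it deals with cell mix.

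**The predicted shift is narrow.** The documents anticipate changes within CD4 T cells (Treg and Th1:Th2), not a shift of several points in lymphocytes, monocytes or neutrophils. The Discussion speaks of activation of immune cells, not altered counts. This stands. The 5-point case is an outside assumption, and the Treg-type case is closer to the study's own premise.

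**The array may be small.** A reader might apply the numbers planned for the end of follow-up, 270 v 45, and infer that false differences are almost certain: the step 3 inputs then give P<0.05 in 91% to 100% for a 5-point shift. The documents do not support that as the headline, because the array section counts 24 samples. Table 2 lists methylation without a number, so the array size is at best unclear.

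**Adjustment can remove the signal sought.** The Discussion has FOXP3 methylation leading to fewer Treg cells. Conditioning on Treg share then conditions on a proposed consequence. This stands, and it rules out making a Treg-adjusted model the sole or primary analysis. A marker of cell mix may also still predict outcome, which is one of the stated aims.

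**Conclusion.** The point holds as a limit on interpretation. Following the plan as written, a difference in leukocyte composition can be reported as an epigenetic difference, and the planned confirmation cannot tell them apart. The exposure is greatest at cell-specific loci, notably the Treg-specific FOXP3 region.

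A reader might infer that cell-count differences will be mistaken for epigenetic change throughout the results. The documents do not support that: they give no size for any shift, and the shift they predict is confined to T-cell subsets that form a small part of blood DNA.

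Under the step 3 assumptions, with 24 arrays split 12 v 12, a marker with no within-cell change reaches P<0.05 in about 24% to 47% of repeats for a 5-point shift in a major fraction. For a 2-point or Treg-only shift the figure is about 6% to 19%. These are single-marker rates at 0.05. The plan selects regions by FDR, so they illustrate the mechanism and do not forecast how many false regions will be declared. With more arrays the rates rise, as the 300 v 50 column shows.

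**What to change.** In the DNA methylation analysis section:

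1. State the number of arrays and the group split.
2. Obtain each probe's P value from a regression of methylation on group with age and BMI, and carry these into the 1-kb region step.
3. Report the regions side by side with and without adjustment for leukocyte fractions. Take the fractions from the planned cytometry (Table 3 covers CD3/CD4/CD8, CD14, CD15, CD16 and Treg) or estimate them from the array. If only 24 arrays are run, limit the adjustment to a few major fractions or one summary score.
4. Claim a within-cell epigenetic change only for regions that persist after adjustment.
5. At FOXP3, say that Treg share may be a consequence of methylation, so both results are needed and neither alone settles the question.

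No new samples are needed, since Table 2 already schedules cytometry and methylation at the same visits. The cost is a few degrees of freedom, which matters more with 24 arrays than with several hundred, and probably fewer regions.
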